### Data collection

To assess the comparability of the study groups, baseline demographic and medical information will be collected at the time of entry into the study. The baseline assessment will include maternal age, socio-demographic data, smoking and alcohol use, infections during pregnancy, allergies, use of vitamins/supplements/probiotics in the previous month, history of prior pregnancies and lactations including previous mastitis and breastfeeding duration, and recent use of antibiotics. This information will be obtained from the participant and/or her medical record.

At the time of discharge, data related to the birth and infant feeding will be collected to evaluate the impact of events and outcomes around the time of birth on infant feeding practices. This information will be ascertained from both the participant and medical records and will include site, gestation at birth, mode of birth, antibiotics during labour, birth or postpartum, complications of birth, length of hospital stay and initiation of infant feeding. Baseline infant data on general characteristics and well-being will also be collected. This will include information on infant sex, birthweight, Apgar scores at 1 and 5 min, resuscitation and any morbidity and will be obtained from the infant’s medical record.

Follow-up questionnaires will be used to evaluate long term maternal and infant secondary outcomes as detailed above with timing and method of collected data presented in Table 1.

**Table 1 Tab1:** Timing of data collection for the APProve trial

Peripartum Period	Intervention	Timing
Birth (1–72 h)	Identification of eligible women	≥37 weeks’ gestation
	Patient information given, consent, baseline data collected	

Postnatal (Birth to 8 weeks)	Data collection of treatment compliance, breast pain, infection symptoms and infant feeding	Daily x 56 (APP/calendar diary)
	Data collection of well-being, Drs’ visits, and medication intake	Weekly x 8 (APP/email)
Postnatal (2,6 & 12 months)	Follow up questionnaire (post, email or APP)	2 months postpartum
	Follow up questionnaire (post, email or APP)	6 months postpartum
	Final follow up questionnaire (post, email or APP)	12 months postpartum

### Independent assessment of intervention and mobile phone application system

A separate sub-study will be conducted to assess the independent effect of the probiotic without the potential influence of the APProve-Lite system. Despite the APP being a tool to facilitate data collection and improve compliance, it may be viewed as an intervention in itself, and have an unintended effect on study outcomes. Assessment of the APP is important to ensure this tool does not bias or exert any influence on study outcomes. This will involve a sub-study utilising a pragmatic and ‘standard follow-up’ approach to data collection and follow-up of women throughout the trial for collection of information on symptoms related to study outcomes and ensuring compliance with the ingestion of the intervention.

The sub-study will involve a sample of 100 women who will be recruited on randomly selected days of each month. These women will be recruited and enrolled into the trial in an identical way to those of the APP group and randomised to the intervention as in the main study. However, they will not be asked to use the APP throughout the trial. Rather, these women will be provided with a 2-month calendar diary to complete each day. They will be encouraged to place this in a visible location such as on the fridge to encourage daily compliance. Here they will record daily ingestion of the probiotic and symptoms via check boxes (daily survey). They will be provided with an addressed reply-paid envelope in which to post the completed diary back to the recruiting center. Each week, women will be emailed a link to an online Survey Monkey questionnaire to complete (weekly survey). At the end of the intervention, women will be emailed a web-link to the 2, 6 and 12-month follow-up questionnaires.

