### Sample size

Given the lack of evidence related to the potential effect of probiotic use for the prevention of mastitis, we used the results from the comparable trials of antibiotics for the prevention of mastitis to determine effect sizes. Although the Cochrane review reported an overall 57% non-significant reduction in mastitis [24], with individual trials finding an up to 76% reduced risk [25], we chose a more conservative 50% reduction as a clinically meaningful treatment effect. Based on an expected rate of mastitis in the control group of 18% [9–11], two-sided 5% significance level and a power of 80%, we estimated a total sample size of 452 would be required. However, given studies related to the duration of breastfeeding report a cessation rate in the first 8 weeks post-partum of up to 20% [9, 15], and a potential loss-to follow-up of 5–10% may occur with withdrawals or non-compliance, we inflated the sample size by a further 30% to ensure complete data. Hence, we estimated a total sample size of approximately 600 women would be required (300 per group) for this trial, including all sites.

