### Statistical analyses

The analysis and reporting of the results will follow the CONSORT guidelines (http://www.consort-statement.org/). Primary and secondary outcomes will be analysed using an intention-to-treat approach, which includes all losses-to follow-up, non-compliances or withdrawals. Baseline characteristics will be compared between allocated treatment groups using frequencies and descriptive statistics. The principal analysis will use an unadjusted Chi-Square test to compare the incidence of mastitis between the two groups. The corresponding unadjusted relative risk with 95% confidence interval will also be calculated. Further analysis of the primary outcome will use multivariable logistic regression to examine the effect of adjusting for any imbalances at baseline or important predictors of mastitis (e.g. previous history of mastitis, antibiotic use, cracked nipples, or duration of breastfeeding). Additional unadjusted and adjusted analyses of all secondary outcomes will be performed using measures and multivariable models appropriate for the outcome. An analysis of women compliant with treatment (per protocol) will also be performed to assess the robustness of the primary findings. For all analyses, the number of cases with complete data and those with missing values will be reported. If necessary, reason for and type of missing data will be assessed to determine whether multiple imputation, sensitivity analysis or other approaches (“best” and “worst” case scenario, last value carried forward) will be required. Analyses will be performed using SPSS Version 24 (IBM SPSS Statistics, 2016 IBM Corporation, Chicago, IL) by an analyst not involved in any data collection and blinded to treatment allocation.

To assess the impact of the APP, the rate of primary and secondary study outcomes will be compared between the main study group and small sub-sample. Compliance rates in the ingestion of the intervention, and completeness and acceptability of data collected during daily and weekly follow-up will also be examined between the two study groups.

This protocol has been formatted according to the SPIRIT (Standard Protocol Items: Recommendations for Interventional Trials) guidelines (Additional file 1).

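### The sub-study promises the probiotic effect without the APP, but the only stated analysis compares outcome rates by follow-up mode, and 100 women can settle neither this aim nor the absence of APP influence

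*Protocol article*

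**What the plan says.** The Protocol article, under Independent assessment of intervention and mobile phone application system, gives the sub-study two purposes.

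- The first is the treatment effect free of the APP: "A separate sub-study will be conducted to assess the independent effect of the probiotic without the potential influence of the APProve-Lite system".
- The second is reassurance about the APP itself: "Assessment of the APP is important to ensure this tool does not bias or exert any influence on study outcomes".

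The size is fixed without justification: "The sub-study will involve a sample of 100 women who will be recruited on randomly selected days of each month". These women are enrolled and randomised to probiotic or placebo like the others, but use a calendar diary and emailed surveys in place of the APP.

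Under Statistical analyses, the impact of the APP is to be assessed as follows: "the rate of primary and secondary study outcomes will be compared between the main study group and small sub-sample". Compliance, and the completeness and acceptability of the data, are also compared between the two groups. The article names no probiotic-versus-placebo contrast within the sub-sample, no arm-by-mode interaction and no equivalence margin. The Sample size section covers the whole trial only.

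**The concern.** The first purpose is a treatment contrast: probiotic against placebo among women who do not use the APP. Whether the APP alters that effect is an arm-by-mode question. The stated analysis is a contrast between modes. It answers a third question, namely whether outcome levels differ between APP users and non-users.

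These quantities can diverge completely. Suppose APP women have mastitis rates of 18% on placebo and 9% on probiotic, and non-APP women have 13.5% in both arms. Each mode then averages 13.5%, so the stated comparison shows no difference although the probiotic works only alongside the APP.

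The second purpose is worded as assurance. With no margin and a small sample, failing to find a difference cannot give that assurance. The protocol itself recognises that the APP could act as an intervention, and this sub-study is the check it offers. The check should therefore estimate what it claims to estimate and be described at the strength it can bear.

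**Working it through.** **Inputs (Protocol article, Sample size, unless noted).** Control rate 18%; a 50% relative reduction, so 9% on probiotic; two-sided 5% level; 80% power; 600 women in total, 1:1. Sub-study of 100 women (Independent assessment section). Assumptions: about 50 per arm, because stratification is by previous mastitis and not by mode; the 100 lie within the 600, leaving 500 APP women, about 250 per arm; full data on everyone, which is the favourable case.

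**1. The protocol's own figure.** The plan states: "two-sided 5% significance level and a power of 80%, we estimated a total sample size of 452 would be required". Pooled-variance formula, with mean rate (0.18 + 0.09)/2 = 0.135:

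n per arm = [1.96·√(2·0.135·0.865) + 0.8416·√(0.18·0.82 + 0.09·0.91)]² / 0.09²
= [1.96·0.4833 + 0.8416·0.4791]² / 0.0081 = 1.3504² / 0.0081 = 225.1, rounded up to 226.

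The total is 452, an exact match, so the same method is used for the power calculation below.

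**2. Probiotic effect within the non-APP women, 50 per arm.**

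- Null SE = √(2·0.135·0.865/50) = 0.0683. Alternative SE = √((0.1476 + 0.0819)/50) = 0.0677.
- Power = Φ[(0.09 − 1.96·0.0683)/0.0677] = Φ(−0.649) = 25.8%.
- Exact enumeration gives 27.3% for the chi-square test and 16.5% for Fisher's test.
- With 40 evaluable per arm, power is 21.5%; with 35, it is 19.3%.
- Expected events are 9 v 4.5. SE(log RR) = √(0.82/9 + 0.91/4.5) = 0.542, and exp(1.96·0.542) = 2.89. An observed RR of 0.50 therefore has a 95% CI of 0.50/2.89 to 0.50·2.89, which is 0.17 to 1.45.

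**3. The stated comparison by mode, 500 v 100, average rate 13.5%.**

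- SE = √[0.135·0.865·(1/500 + 1/100)] = 0.0374.
- 95% CI half-width = 1.96·0.0374 = 7.3 points, which is 7.3/13.5 = 54% of the average rate.
- Difference detectable with 80% power = 2.80·0.0374 = 10.5 points.
- If the 100 were additional (600 v 100), the half-width would be 7.2 points.

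**4. Does the APP modify the probiotic effect? Ratio of relative risks between modes.**

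- Variance of log RR: 0.2933 in the sub-sample (50 per arm) and 0.2933/5 = 0.0587 in the main group (250 per arm).
- SE = √(0.2933 + 0.0587) = 0.593; exp(1.96·0.593) = 3.2. The 95% CI runs from the estimate divided by 3.2 to the estimate multiplied by 3.2.
- If the true RR were 0.5 with the APP and 1.0 without it (18% in both non-APP arms), the variance would be 2·0.82/9 + 0.0587 = 0.2409 and the SE 0.491. Power = Φ(0.693/0.491 − 1.96) = Φ(−0.548) = about 29%.

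**The case against.** The strongest reply is that the comparison by mode is not misplaced. An APP that acts as an intervention could raise or lower outcome levels in both arms. Comparing rates by mode is the direct way to look for that, and the Statistical analyses section presents it for that purpose. This stands. A reader might infer that the stated analysis answers neither purpose and should be replaced by an interaction. The text does not support that, and the interaction alone would remove the analysis that serves the second purpose while being no more conclusive.

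Other stronger readings also go too far.

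- *The 26% contradicts the plan.* It does not. The article claims no power for the sub-study and calls the group a small sub-sample. The figure is derived.
- *The plan pools the arms.* Combining them is the natural reading of the sentence, but the text does not say so, and a fuller analysis plan may report rates by arm.
- *Choosing mode by recruitment day biases the comparison.* The days are to be selected at random, and nothing in the document demonstrates an imbalance.
- *The compliance comparison rests on different instruments.* Daily reporting does differ (APP or diary), but the Intervention section also collects unused sachets at eight weeks without restriction by mode.
- *The non-APP women might fall outside the principal analysis.* They are enrolled, randomised and covered by the intention-to-treat statement.
- *A null result will be reported as proof.* No decision rule says so. The word *ensure* sits in a sentence about why the assessment matters.

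Finally, women in both modes are randomised to probiotic or placebo, so mode is not a rival explanation for the principal comparison. This is correct and limits the weight of the point. What the reply does not meet is the first stated purpose, for which no matching analysis is given, or the low precision for either purpose. A separate analysis plan could add the missing contrast, but it would not by itself correct the stated claim or enlarge the 100.

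**Conclusion.** The point holds for a secondary component of the trial. One stated purpose of the sub-study, the probiotic effect without the APP, has no corresponding analysis in the article. The analysis that is stated serves the other purpose in part. Neither can be met conclusively with 100 women: about 26% power for the treatment effect, an uncertainty of about ±7.3 points in the rate difference by mode, and a factor of about 3.2 each way in the ratio of relative risks.

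These sizes rest on 18% v 9%, a near-even split by arm within mode, the 100 being part of the 600, and complete data. Losses would widen every interval. The 600 v 100 reading hardly alters the mode comparison. The principal analysis and the main sample size are not called into question.

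**What to change.** In the Statistical analyses section, keep the comparison of outcome rates by mode, with a 95% CI for the difference. Add, in all randomised women, the probiotic-versus-placebo relative risk within each mode and the arm-by-mode ratio of relative risks, each with a 95% CI.

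In the section on the sub-study, describe it as exploratory. Replace the wording about ensuring no influence with a statement that the influence of the APP on outcome levels and on the probiotic effect will be estimated, and that a non-significant difference will not be read as absence of influence.

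The cost is one extra model, some rewording and a more modest claim. No further participants or data are needed. Keeping a claim of no influence would instead require an equivalence margin and a sample size to match.

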### Data monitoring committee

The data monitoring committee (DMC) will be established to monitor the trial and review the study progress. The DMC will meet once half way through trial recruitment to review the safety data and monitor the progress of the trial. There will be only one analysis at the end of the trial. The Committee members will be independent of the trial, free of conflicts with any of the investigative team. The terms of reference and functions are derived from the principles established by the Data and Safety Monitoring Boards: Lessons, Ethics, Statistics Study Group charter. The DMC will report its recommendations directly to the Trial Steering Committee, who are the authors of this protocol.

### Adverse event reporting

#### Adverse event

Side effects of the probiotic will be collected via the 2-month questionnaire. Mild gas and bloating are the only known reported side effects of *Lactobacillus fermentum*. Reported incidents will be reported to the DMC for review.

#### Serious adverse event

Any maternal or infant deaths will be reported to the ethics committee as required and reviewed by the DMC.

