## Background

Breastfeeding has been consistently shown to be protective against a broad range of immediate and long term infant and maternal health outcomes [1–3]. International guidelines recommend exclusive breastfeeding for all babies in the first 6 months of life as it provides the best nutritional start for infants and promotes their healthy growth and development. Given the positive benefits of breastfeeding, it is of concern that the 2010 Australian Institute of Health and Welfare (AIHW) National Health Survey reported less than 15% of women exclusively breastfeeding at 5 months of age, despite a 96% initiation rate at birth [4]. These findings suggest that more resources and research are required to identify and treat the underlying causes of breastfeeding cessation in order to extend the overall duration and improve long term maternal and child health outcomes.

Mastitis and the pain associated with the condition have been shown to be associated with the cessation of breastfeeding [5–7]. The World Health Organisation (WHO) defines mastitis as an inflammatory condition of the breast, which may or may not be accompanied by infection [8]. It occurs in 15–21% of breastfeeding mothers in Australia [9–11]. Most episodes occur in the first 6–8 weeks postpartum but can occur at any time during breastfeeding [12]. Almost one-third of women experience a recurrent episode [13–15], and up to 3% of women with mastitis develop a breast abscess, often necessitating hospitalisation [16, 17].

Little is known about the epidemiology and pathogenesis of this common condition [7]. Though not well described, the risk factors appear to be associated with milk stasis, nipple damage and maternal fatigue [8, 9]. Cracked nipples may facilitate entrance of microorganisms through the skin, and incomplete emptying of the breasts may result in milk stasis which provides a susceptible and receptive culture media for microorganisms. Decreased immunity and a lowered resistance to infection may be a result of maternal fatigue [8, 18–20]. Other risk factors include a history of mastitis with a previous child, using an antifungal nipple cream and using a manual breast pump [7, 21].

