### Setting

The study will be conducted at the Royal North Shore Hospital, Northern Sydney Local Health District (LHD); the Royal Prince Alfred Hospital, Sydney LHD; and the Royal Hospital for Women, South Eastern Sydney LHD; in New South Wales, Australia. The annual number of births at each site are 2600, 5000 and 5000, respectively. Ethics approval for this study has been given by the Northern Sydney Local Health District Human Research Ethics Committee: HREC/14/HAWKE/358 with site specific governance approval provided prior to commencement from each site. The trial is registered with the Australian New Zealand Clinical Trials Registry: ACTRN12615000923561 and conducted according to standardised Good Clinical Practice guidelines.

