#### Suspected unsuspected serious adverse reaction (SUSAR)

We do not anticipate any SUSARs in relation to this trial.

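### The serious-event rule names only deaths and side effects are asked once at 2 months, so non-fatal admissions have no stated prompt reporting route and transient side effects may be missed

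*Protocol article*

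**What the plan says.** All references are to the protocol article.

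- **Serious adverse event.** The section reads in full: "Any maternal or infant deaths will be reported to the ethics committee as required and reviewed by the DMC". No other kind of event is named.
- **SUSAR.** "We do not anticipate any SUSARs in relation to this trial". No procedure is given in case one occurs.
- **Adverse event.** "Side effects of the probiotic will be collected via the 2-month questionnaire". The section adds that "Reported incidents will be reported to the DMC for review", with no limit on severity and no time limit.
- **Data monitoring committee.** "The DMC will meet once half way through trial recruitment to review the safety data and monitor the progress of the trial". What counts as safety data is not defined.
- **Outcome measures and Follow-up.** Adverse effects of treatment are a secondary maternal outcome. Infant hospital admissions, and hospital or doctor visits generally, are self-reported at 2, 6 and 12 months.
- **Intervention and Table 1.** During the 8 weeks of treatment, daily forms (56) cover intake, breast pain, infection symptoms and feeding. Weekly forms (8) cover well-being of mother and infant, unscheduled doctor's visits and medication.
- **Hypotheses.** The app is expected to reduce recall bias.

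**The concern.** The article gives separate subsections to adverse events, serious adverse events and SUSARs, so these are stated rules and not merely gaps in a condensed text. Followed as written, they have three weaknesses.

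1. A life-threatening illness or a hospital admission, in the mother or in the newborn she is breastfeeding, triggers no stated prompt report. The trial would learn of an admission mainly as an outcome item on a later questionnaire.
2. A secondary outcome, adverse effects of treatment, rests on one enquiry at the end of treatment. The known effects are mild gas and bloating, which a woman could well have forgotten some weeks later. A woman who has left the trial may not complete the form at all.
3. The one scheduled DMC meeting comes too early to see much of the side-effect data.

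At stake are how quickly a non-fatal safety problem would be noticed under a live bacterial product, and how complete the tolerability data would be.

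**Working it through.** **Reproducing the plan's figure.** The only calculated figure in the plan is the sample size of 452. With 18% against 9%, two-sided 5% and 80% power, the pooled-variance formula without continuity correction gives n per arm = [1.96·√(2·0.135·0.865) + 0.842·√(0.18·0.82 + 0.09·0.91)]² / 0.09² ≈ 225.1, rounded up to 226, so 452 in total. It reproduces, and it does not bear on this point.

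**Step 1: what is captured, and where it is sent.**

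| Event | Where and when captured | Stated safety route |
|---|---|---|
| Death of mother or infant | Serious adverse event section | Ethics committee and DMC |
| Infant hospital admission | Self-report at 2, 6, 12 months | None stated |
| Hospital or doctor visits | Self-report at 2, 6, 12 months | None stated |
| Infection symptoms, breast pain | Daily for 8 weeks | None stated |
| Well-being, unscheduled doctor's visits, medication | Weekly for 8 weeks | None stated |
| Side effects of the probiotic | 2-month questionnaire | DMC, timing not stated |
| SUSAR | None anticipated | None stated |

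Death is the only event for which both the ethics committee and the DMC are named. Non-fatal serious events can appear in several data streams, but none of those streams is tied to prompt reporting.

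**Step 2: recall window for side effects.** Treatment starts within days of birth and lasts 8 weeks, and the form is due at 2 months. An effect confined to week 1 is recalled about 8 − 1 = 7 weeks later. With the existing weekly form the recall window would be at most 1 week.

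**Step 3: women who may not return the form.** The Sample size section allows for 5–10% loss through withdrawal or non-compliance. Of 600 women that is 600 × 0.05 = 30 to 600 × 0.10 = 60. The document does not say how many of these would stop because of side effects, or how many would still return the form. This is the number at risk of being missed, not an estimate of missed side effects.

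**Step 4: forms due after the DMC meeting.** Inputs: 600 women; one meeting at half recruitment, so 300 recruited; a form due about 2 months after entry, since entry is within 72 h of birth.

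- Women recruited after the meeting: 600 − 300 = 300, or 50%. All their forms fall due after it.
- Women recruited in the 2 months before the meeting are also not yet due. The recruitment period is not stated. Assuming a constant rate over M months, they number 600 × 2/M, and the share of forms due after the meeting is 0.5 + 2/M.

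| Assumed M | Not yet due at meeting | Total due after meeting | Share |
|---|---|---|---|
| 12 months | 100 | 400 | 67% |
| 24 months | 50 | 350 | 58% |
| 36 months | 33 | 333 | 56% |

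The floor of about 50% follows from the plan's own figures. The excess above it depends on the assumed M.

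**The case against.** The strongest reply is that the article is a condensed text. Its serious-event sentence says what happens to deaths; it does not say that other events are excluded. Reported incidents go to the DMC without a severity limit or a cut-off date, and the DMC works to separate terms of reference that may allow ad hoc review. Daily and weekly forms could bring a serious infection or illness to light during treatment. Earlier postpartum studies reported no major side effects, so a single enquiry at the end of treatment may be thought proportionate.

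Much of this stands, and it rules out several stronger readings that a reader might infer:

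- **That admissions escape safety review.** Not shown. The safety data put to the DMC are undefined and could include them. What is missing is a stated prompt route.
- **That side effects will be under-counted, or that the arm comparison will be biased in a known direction.** Not shown. The article gives no side-effect rate, recall loss or differential drop-out, and in a double-blind trial recall loss may well be similar in both arms.
- **That the rule contradicts the claim to be** "conducted according to standardised Good Clinical Practice guidelines"**.** The document does not set out that standard's definition of a serious event, so no internal contradiction can be demonstrated.
- **That abscess admissions form a hidden safety signal.** The Background says up to 3% of women with mastitis "develop a breast abscess, often necessitating hospitalisation". That gives at most 600 × 0.135 × 0.03 ≈ 2.4 abscesses (18% and 9% averaged), or 600 × 0.18 × 0.03 ≈ 3.2 with no treatment effect. These are upper bounds, not every case is admitted, and abscess is already a secondary outcome, so it will be counted.

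The reply does not dispose of the core. A section headed for serious events names only deaths, and one questionnaire is the only instrument named for side effects. The weekly items are not described as side-effect collection and have no stated safety route.

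**Conclusion.** The point holds as a worthwhile, inexpensive improvement to safety reporting; it does not threaten the design, the sample size or the primary analysis.

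- Non-fatal serious events in mother or infant have no stated prompt route to the ethics committee or the DMC.
- Collecting side effects once, with recall of up to 8 weeks, risks missing early, transient effects and effects in women who withdraw. The size and direction of any loss cannot be derived from the document.
- At least about half of the 2-month side-effect forms fall due after the only scheduled DMC meeting (56–67% if recruitment runs at a constant rate over 36 down to 12 months, which is an assumption).

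The conclusion rests on reading the safety sections as the operative rules. If the full protocol or the DMC's terms of reference already provide a wider route, the first and third items reduce to a wording change in the article.

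**What to change.** 1. Add side-effect items to the existing weekly questionnaire, in both the app and the emailed web-link form. Keep the 2-month question as a final check.
2. Extend the serious-event reporting wording beyond deaths to life-threatening events and to hospital admissions of mother or infant during the intervention, with prompt reporting to the ethics committee and the DMC.
3. State that events arising after the mid-recruitment meeting are sent to the DMC as they occur, and say which data make up the safety data it reviews.

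The cost is some protocol wording, a few more items for participants each week, and extra logging, since some postpartum admissions are to be expected whatever the treatment.
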